#### Secondary endpoint

The secondary endpoint is the comparative analysis of diagnostic accuracy between Sonazoid-CEUS and CECT in a single lesion. When the results show that Sonazoid-CEUS provide better diagnostic efficacy than CECT, the study will be considered to be successful because it means the data collected in the present Sonazoid-CEUS could be a potential diagnostic tool instead of CECT despite the good diagnostic performances achieved by the latter.

#### Tertiary endpoint

The tertiary endpoint includes a detection rate of any adverse event related to Sonazoid-CEUS. The adverse event rate is defined as the proportion of patients having an adverse event following injection of Sonazoid out of the patients enrolled in the study. Short-term and long-term adverse events are to be recorded according to the Common Terminology Criteria for Adverse Events (CTCAE version 4.0) (16) with telephone interviews 3 and 30 days after KPWLSM, the patient with adverse events will be recalled to the hospital for further data collection. The study group will discuss each adverse event based on patient's medical history as to see if the adverse event is similar to that of other ultrasound contrast agents like SonoVue.

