### I (intervention)

All patients will receive the examinations of Sonazoid-CEUS, conventional ultrasound and contrast-enhanced MRI (CEMRI), and 65 of them should have additional CECT scans.

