### Schedule of the study

After obtaining informed consent, the study group will check both of the inclusion and exclusion criteria, participants' background and pregnancy status. Four training cases and 330 formal cases were included consecutively, and all subjects will be subjected to conventional ultrasound, Sonazoid-CEUS, CEMRI examinations, 65 of which should also be subjected to CECT examinations.

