### After inclusion

This study is divided into radiological examination (CECT/CEMRI) and ultrasound examination (conventional ultrasound and KPWLSM). Both parts are completed independently in a blind state of reading images and filling out the case report forms (CRFs). Either radiological or ultrasound examination start first is all right, and the interval between the two examinations is required from 24 h to 60 days.

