#### Sample size

As sample size calculation is closely related to research design, and this study consists of several parts which involves the comparison of superiority and diagnostic accuracy, so the calculation of multiple sample sizes is carried out, followed by the larger size as the final calculation results.

For the comparison of superiority and diagnostic accuracy between conventional ultrasound and Sonazoid-CEUS, we assumed a 25–50% prevalence of liver metastatic lesions in our target population (17), while 62.5–87.7% of sensitivity, 40–60% of specificity in conventional ultrasound (12), and 73–95% of sensitivity, 65–75% of specificity in Sonazoid-CEUS according to previous literature studies (18, 19). Also, a 10% dropout rate is included, and the required number of subjects is calculated to be 330.

For the comparison of superiority and diagnostic accuracy between CECT and Sonazoid-CEUS, we also assumed a 25–50% prevalence of liver metastatic lesions in our target population, while 90% of sensitivity in CECT (19), and 73–95% of in Sonazoid-CEUS according to previous literature studies. Since no AUC has been reported, this study attempted to use AUC of 0.75, 0.85, 0.95 for sample size calculation, and a 10% dropout rate is included. The required number of subjects for this part is calculated to be 65.

The sample size was calculated on the non-parametric module of PASS software using paired non-parametric test. With all these assumptions, a minimum of 330 patients are needed to obtain 80% or 90% statistical power for non-parametric test with an α equal to 0.05, of which at least 65 cases need to have received CECT.

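### The adverse event rate divides events after Sonazoid injection by all patients enrolled, so it is correct only if every enrolled patient is injected and can otherwise only be too low

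*Protocol article*

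**What the plan says.** The Tertiary endpoint section of the protocol article names what is to be measured: "The tertiary endpoint includes a detection rate of any adverse event related to Sonazoid-CEUS". It then fixes the rate as "the proportion of patients having an adverse event following injection of Sonazoid out of the patients enrolled in the study".

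Exposure is planned for everyone. Under I (intervention), the article states: "All patients will receive the examinations of Sonazoid-CEUS, conventional ultrasound and contrast-enhanced MRI (CEMRI"). Schedule of the study says the same of all subjects and gives the numbers: "Four training cases and 330 formal cases were included consecutively".

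Four other places bear on whether a patient can be enrolled without being injected:

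- **Schedule of the study:** "After obtaining informed consent, the study group will check both of the inclusion and exclusion criteria, participants' background and pregnancy status".
- **After inclusion:** "Either radiological or ultrasound examination start first is all right, and the interval between the two examinations is required from 24 h to 60 days".
- **Stopping rule:** a patient may withdraw or take back consent, and the researchers may discontinue a patient on medical grounds.
- **Sample size:** "Also, a 10% dropout rate is included, and the required number of subjects is calculated to be 330".

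The Data analysis section, by contrast, defines the efficacy population by the examinations actually received. The article defines no corresponding population of injected patients for safety.

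**The concern.** A patient who never receives Sonazoid cannot have an adverse event after receiving it. Such a patient adds one to the denominator and can add nothing to the numerator, so the reported figure is no longer the risk among those exposed. The error has only one possible direction, the reassuring one.

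The definition is written out explicitly, so this is a stated rule and not a detail left to a fuller document. It governs the only safety endpoint in the article, for an agent that the trial hopes to support as a screening tool. What is at stake is the accuracy of one descriptive percentage. Sample size, significance level, power, and the primary and secondary comparisons do not depend on it.

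**Working it through.** **Inputs from the article**

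- Enrolled: E = 330 formal cases (Schedule of the study; Sample size).
- Assumed dropout: 10% (Sample size).
- Expected adverse event rate: none is given. The rates and counts below are assumptions for illustration.
- Number enrolled but not injected: none is given, so it is varied.

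**Step 1. The plan's own figure.** The 330 is consistent with a 10% allowance in either of two common forms: 297 / (1 − 0.10) = 330, or 300 × 1.1 = 330. The implied loss is therefore 33 of 330 (10.0%) or 30 of 330 (9.1%). The larger is used as the ceiling. The completer number cannot be derived uniquely, because the sample size inputs are ranges; this point does not need it.

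**Step 2. The formula.** Let I be the number injected and A the number with an adverse event after injection.

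- Rate as defined: A / E
- Rate among those exposed: A / I
- Ratio: (A / E) / (A / I) = I / E
- Relative understatement: 1 − I / E = (E − I) / E, the uninjected share of those enrolled

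Since I cannot exceed E, the ratio cannot exceed 1. The error is zero when I = E and downward otherwise.

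**Step 3. Size over the possible range**

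| Not injected | Injected | Relative understatement | True 1% reported as | True 5% reported as | True 10% reported as |
|---|---|---|---|---|---|
| 0 | 330 | 0% | 1.00% | 5.00% | 10.00% |
| 3 | 327 | 0.9% | 0.99% | 4.95% | 9.91% |
| 10 | 320 | 3.0% | 0.97% | 4.85% | 9.70% |
| 17 | 313 | 5.2% | 0.95% | 4.74% | 9.48% |
| 33 | 297 | 10.0% | 0.90% | 4.50% | 9.00% |

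In the last row the absolute shift is 0.1, 0.5 and 1.0 percentage points.

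**Step 4. An illustrative count.** With nine patients having events, 9 / 330 = 2.7% and 9 / 297 = 3.0%. The exact two-sided 95% intervals are 1.3% to 5.1% and 1.4% to 5.7%. Even at the ceiling, the 0.3-point shift is small against the sampling uncertainty.

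**Step 5. Can E and I differ?** Nothing in the article says that they will. Radiology may come first, with up to 60 days before ultrasound, and withdrawal is allowed at any time, so a patient can leave in between. Consent also precedes the eligibility and pregnancy checks. The article does not define enrolled; if it were counted from consent, screen failures would enter the denominator too. No figure is given for those, and they are not in the table.

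**The case against.** The strongest reply is that the protocol plans Sonazoid-CEUS for everyone, so enrolled and injected are the same group and the rate is right as written. As a description of the design, that stands. A reader might infer from the definition that the endpoint is understated, or that the rule always biases the rate. The article does not support either reading, because it nowhere says that any enrolled patient goes uninjected.

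Three further objections stand in part:

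- **The 10% is not a forecast of uninjected patients.** It is an allowance in the sample size for the efficacy comparisons. It may equally cover losses after injection, such as an MRI or CT not completed or reference follow-up missing. It serves here only as a ceiling.
- **The 60-day window is an imperfect mechanism.** It separates the two examinations, not enrolment from injection. Inclusion criteria admit patients whose MRI or CT is already done, and ultrasound may come first. The window permits a departure before injection but does not make one likely.
- **The effect is small and no decision turns on it.** The endpoint is tertiary and, unlike the primary and secondary endpoints, carries no success criterion.

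Two other tempting readings also go too far. One is that the upper confidence limit would be too low; the Tertiary endpoint section specifies no confidence limit. The other is that the four training cases are exposed but left out of the rate. The article counts them separately from the formal cases but says they were included consecutively, and it does not say whether they enter the rate. Leaving out exposed patients together with their events would not in itself push the rate down.

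None of this justifies keeping the denominator. If everyone is injected, the corrected definition gives the same result. If not, only the corrected one gives the risk among those exposed.

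**Conclusion.** The point holds in conditional form. The definition pairs a numerator restricted to injected patients with a denominator of everyone enrolled. It gives the right answer only if every enrolled patient is injected; otherwise it errs downward by the uninjected share. On 330 enrolled, that is 0% with none uninjected, 3% relative with 10, and 10% relative if the whole assumed dropout preceded injection.

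The ceiling rests on three assumptions: 330 are enrolled, losses do not exceed the stated 10%, and screen failures are not counted as enrolled. The event rates are illustrative only. This is a minor but genuine defect in a descriptive safety endpoint, worth correcting because its only possible error is in the reassuring direction.

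**What to change.** Replace the definition in Tertiary endpoint with: the number of patients with at least one adverse event after Sonazoid injection, divided by the number of patients who received at least one Sonazoid injection. Counting patients, not injections, also covers those in whom the CEUS examination is repeated.

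Add two statements:

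- The number of patients enrolled but not injected will be reported.
- Whether injected training cases are counted, with the same answer for numerator and denominator.

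An exact 95% confidence interval would be a useful but optional addition.

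The cost is a sentence or two in the plan. It requires that the case report form show for each patient whether Sonazoid was given. The article does not say so explicitly, but the CEUS examination is recorded on that form, so little or no extra data collection should be needed. Sample size and the other endpoints are untouched.

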#### Stopping rule

The patient offers to withdraw.

The subject requested the withdrawal of informed consent.

From a medical point of view, the researchers considered it necessary for the subjects to discontinue the study, etc.

#### Sample size

As sample size calculation is closely related to research design, and this study consists of several parts which involves the comparison of superiority and diagnostic accuracy, so the calculation of multiple sample sizes is carried out, followed by the larger size as the final calculation results.

For the comparison of superiority and diagnostic accuracy between conventional ultrasound and Sonazoid-CEUS, we assumed a 25–50% prevalence of liver metastatic lesions in our target population (17), while 62.5–87.7% of sensitivity, 40–60% of specificity in conventional ultrasound (12), and 73–95% of sensitivity, 65–75% of specificity in Sonazoid-CEUS according to previous literature studies (18, 19). Also, a 10% dropout rate is included, and the required number of subjects is calculated to be 330.

For the comparison of superiority and diagnostic accuracy between CECT and Sonazoid-CEUS, we also assumed a 25–50% prevalence of liver metastatic lesions in our target population, while 90% of sensitivity in CECT (19), and 73–95% of in Sonazoid-CEUS according to previous literature studies. Since no AUC has been reported, this study attempted to use AUC of 0.75, 0.85, 0.95 for sample size calculation, and a 10% dropout rate is included. The required number of subjects for this part is calculated to be 65.

The sample size was calculated on the non-parametric module of PASS software using paired non-parametric test. With all these assumptions, a minimum of 330 patients are needed to obtain 80% or 90% statistical power for non-parametric test with an α equal to 0.05, of which at least 65 cases need to have received CECT.

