### Data analysis

A commercially available software package (SAS version 9.2, SAS Analytics, Marlow, UK) will be used for all the statistical analysis, and the significance level was 0.05 for two-sided tests. Descriptive data will be mainly used in the study. Efficacy analyses of sensitivity, specificity, positive predictive value, negative predictive value and accuracy will be performed using the efficacy population including subjects who received Sonazoid-CEUS, conventional ultrasound, CECT and CEMRI in screening liver metastases.

For the comparison of superiority among Sonazoid-CEUS, conventional ultrasound and CECT, intra-individual comparison will be made in terms of the detection rate of the number of detected liver metastatic lesions with pared-samples *T*-test. And the Chi-square test or Fisher exact test will be used to compare the diagnostic accuracy of the three imaging modalities in screening liver metastases.

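### The 65 CECT patients are sized on AUC with a paired test, but diagnostic accuracy is analysed as a proportion by chi-square or Fisher test, so the stated power does not carry over

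*Protocol article*

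**What the plan says.** The secondary endpoint is the "comparative analysis of diagnostic accuracy between Sonazoid-CEUS and CECT in a single lesion".

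The Sample size section gives these inputs for that part:
- Prevalence and CECT sensitivity: "we also assumed a 25–50% prevalence of liver metastatic lesions in our target population, while 90% of sensitivity in CECT (19".
- Sonazoid-CEUS sensitivity of 73–95%.
- AUC: "Since no AUC has been reported, this study attempted to use AUC of 0.75, 0.85, 0.95 for sample size calculation", with a 10% allowance for dropout.
- Result: "The required number of subjects for this part is calculated to be 65".

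The section closes by naming a paired non-parametric test in PASS, α of 0.05 and power of 80% or 90%. It does not say which AUC belongs to which modality, and it gives no correlation between the two readings.

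The Data analysis section lists its measures: "Efficacy analyses of sensitivity, specificity, positive predictive value, negative predictive value and accuracy will be performed". Its only named test for diagnostic accuracy is chi-square or Fisher exact. The Image assessment section describes readers picking up lesions and agreeing by consensus, and mentions no rating scale.

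**The concern.** The quantity that was sized is not the quantity that is tested. An AUC difference and a difference in proportion correct have different variances. They also have different effect sizes for the same pair of modalities. Accuracy further depends on prevalence and on where each reader draws the line, and the plan leaves prevalence at 25–50%. In addition, the sizing test is paired, whereas chi-square and Fisher tests treat the two readings of one patient as independent.

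The Secondary endpoint section says that a better result for Sonazoid-CEUS here would make it a possible replacement for CECT. That conclusion would rest on about 58 evaluable patients (65 × 0.9 = 58.5), and their stated power describes another test.

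**Working it through.** **Inputs from the article:** AUC 0.75, 0.85, 0.95; prevalence 25–50%; dropout 10%; two-sided α 0.05; power 80% or 90%; N = 65.

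**Supplied by me, because the article does not give them:** the AUC pair, the correlation, equal-variance binormal scores, and one lesion per patient.

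**Step 1. Reproduce 65.** The Hanley-McNeil variance of an AUC A with n₁ diseased and n₀ non-diseased is

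Var = [A(1−A) + (n₁−1)(Q₁−A²) + (n₀−1)(Q₂−A²)] / (n₁n₀), with Q₁ = A/(2−A) and Q₂ = 2A²/(1+A).

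Take 58 patients at 50% prevalence (29 and 29), correlation 0:
- A = 0.75: (0.1875 + 28×0.0375 + 28×0.08036)/841 = 0.00415
- A = 0.95: (0.0475 + 28×0.00226 + 28×0.02314)/841 = 0.00090
- SE of the difference = √0.00505 = 0.0711
- Power = Φ(0.20/0.0711 − 1.96) = Φ(0.85) ≈ 80%

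Fifty-eight is the smallest number reaching 80%, and 58/0.9 = 64.4, rounded up to 65. The match is exact but not unique: the Obuchowski variance with the same pair, 25% prevalence, correlation 0.5 and 80% power also gives 65.

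**Step 2. Could 65 have come from the sensitivities instead?** For a McNemar comparison with independent readings and 80% power, 90% v 73% gives discordant probabilities 0.90×0.27 = 0.243 and 0.10×0.73 = 0.073. Then

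n = (1.96√0.316 + 0.842√(0.316 − 0.17²))² / 0.17² = 83.4,

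so 84 diseased patients. That is 84/0.50 = 168 to 84/0.25 = 336 subjects before dropout. For 90% v 95% the same formula needs 438 diseased. On these assumptions the sensitivities do not give 65, which supports reading it as AUC-based.

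**Step 3. Move the same design to proportion correct, if readings are graded.** With binormal scores, separation is d = √2·Φ⁻¹(AUC), and accuracy at the mid-point cut is Φ(d/2).
- AUC 0.75: d = 0.954, accuracy 0.683
- AUC 0.95: d = 2.326, accuracy 0.878

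An AUC gap of 0.20 becomes an accuracy gap of 0.195 around lower values, where a proportion varies more. Chi-square power with 58 per modality and p̄ = 0.7805:

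Φ[(0.195√58 − 1.96√(2×0.7805×0.2195)) / √(0.683×0.317 + 0.878×0.122)] = Φ[(1.485 − 1.147)/0.569] = Φ(0.59) ≈ 72%.

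Simulation of this design gives about 84–85% for the paired AUC test (DeLong) and about 73% for chi-square or McNemar on accuracy. With uncorrelated scores the paired and unpaired tests give nearly the same power, so this loss comes from the change of scale, not from pairing.

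**Step 4. How far the loss moves (58 evaluable, AUC 0.75 v 0.95).**

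| Assumption | AUC test | Chi-square on accuracy |
|---|---|---|
| 50% prevalence, correlation 0 | 84–85% | about 73% |
| 25% prevalence, correlation 0, mid-point cut | about 72–73% | about 74% |
| 25% prevalence, correlation 0, accuracy-optimal cut | about 72–73% | about 45% |
| 25% prevalence, correlation 0.5, accuracy-optimal cut | about 89% | about 45% |

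If readings are simply yes/no, the empirical AUC is (sensitivity + specificity)/2, which equals accuracy at 50% prevalence. Chi-square for 0.75 v 0.95 is then Φ[(0.20√58 − 1.96√(2×0.85×0.15)) / √(0.75×0.25 + 0.95×0.05)] = Φ(1.10) ≈ 86%, with no loss.

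**Step 5. A 0.10 difference in AUC.** The three listed values also allow 0.75 v 0.85 and 0.85 v 0.95. Hanley-McNeil at 80% power, correlation 0 to 0.5 and 10% dropout needs from 102 patients (0.85 v 0.95, 50% prevalence, correlation 0.5) to 549 (0.75 v 0.85, 25% prevalence, correlation 0). With 58 evaluable, simulated power of the AUC test for 0.85 v 0.95 is about 33–58% over prevalence 25–50% and correlation 0–0.5.

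**The case against.** A reader might infer that the plan throws away graded information and so has clearly less power than intended. The documents do not support that. They nowhere say that the sizing AUCs came from a rating scale, and a yes/no reading also has an AUC. Step 4 shows designs inside the stated prevalence range with no loss. Every power figure beyond the reproduction of 65 rests on a score distribution, cut point and correlation that the article does not give.

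It can also be said that this is a condensed article, so an ROC analysis or a rating item may exist in the full protocol or case report form. That is fair, and absence from the article does not prove absence from the study. Sensitivity, specificity and accuracy are also legitimate measures of diagnostic accuracy, and choosing them is no error. Finally, 65 is a minimum, so more patients may have CECT.

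None of this removes the mismatch. The article states a sizing basis and a test for diagnostic accuracy, and the two differ both in the quantity compared and in pairing. That is a conflict between two stated sections, not a detail left for later.

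**Conclusion.** The point holds as a mismatch: the 80% or 90% power quoted for 65 patients does not describe the chi-square or Fisher comparison of accuracy in the Data analysis section.

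The direction and size of the effect are conditional. If readings are graded, power is probably lower, by about 11 points in the first design that reproduces 65. The range runs from no loss to more than 40 points, depending on prevalence, cut point and correlation. Those figures assume equal-variance binormal scores and one lesion per patient.

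Separately, 65 suits only the widest pairing of the listed AUCs. For a 0.10 difference it is well short of 80% power even with the AUC test, so changing the analysis to AUC would not by itself secure the power. The matter concerns a secondary endpoint, but one on which the plan would base a claim about replacing CECT, and it should be corrected.

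**What to change.** Make the Sample size and Data analysis sections agree.

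**Text-only route.** Drop the AUC basis. Name a paired test of accuracy for Sonazoid-CEUS versus CECT (for example McNemar). State the accuracies assumed for each modality and the assumed agreement between them, and report the power that about 58 evaluable patients give. This costs a paragraph and no data collection.

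**Alternative.** If the same readers record a graded consensus reading for each assessed patient or lesion, make the comparison a paired difference in AUC (DeLong, 95% CI). Keep sensitivity, specificity and accuracy as supporting results, and state which AUC pair and correlation give 65. The rating must also cover patients with no nodule on conventional ultrasound. The Sonazoid-CEUS section picks the target lesion from nodules seen before contrast, so rating target lesions alone would leave those patients out and change both the sample size and the prevalence. The cost is one extra case report form item, unless one already exists, and a measure that is less directly clinical.

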#### Primary endpoint

The primary study endpoint is the comparative analysis of the number of detected liver metastatic lesions among Sonazoid-CEUS, conventional ultrasound and CECT in screening liver metastases. If the results show that Sonazoid-CEUS could detect more lesion than conventional ultrasound and CECT, the study will be considered to be successful because it means the data collected in the present study confirmed the diagnostic improvement provided by Sonazoid-CEUS over conventional ultrasound and CECT, Sonazoid-CEUS will be confirmed as an excellent screening tool without radiation exposure.

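### The 80% or 90% power claimed for 65 CECT patients is not supported on lesion detection, the comparison with CECT that primary success requires

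*Protocol article*

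**What the plan says.** The Sample size section treats the comparison with CECT separately. Its inputs are prevalence ("we also assumed a 25–50% prevalence of liver metastatic lesions in our target population"), sensitivities ("90% of sensitivity in CECT (19), and 73–95% of in Sonazoid-CEUS according to previous literature studies"), 10% dropout and trial AUC values: "Since no AUC has been reported, this study attempted to use AUC of 0.75, 0.85, 0.95 for sample size calculation". The result is given as: "The required number of subjects for this part is calculated to be 65". The section ends by claiming 80% or 90% power at α = 0.05 for a minimum of 330 patients, "of which at least 65 cases need to have received CECT". It names a paired non-parametric method.

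The Primary endpoint section sets the success rule: "If the results show that Sonazoid-CEUS could detect more lesion than conventional ultrasound and CECT, the study will be considered to be successful". Data analysis tests lesion detection within patients by a paired t-test, two-sided at 0.05. The Secondary endpoint section adds a success statement under which CEUS could take the place of CECT.

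**The concern.** Success requires CEUS to detect more lesions than both comparators, so the power of the primary conclusion cannot exceed the power of the CECT leg. That leg rests on the smallest sample in the trial and on the comparator with the highest assumed sensitivity. With CECT at 90%, superiority is false for CEUS values from 73% up to 90%, and the largest assumed advantage is 5 points.

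If the power statement is wrong, the trial may well miss its own success criterion even where CEUS truly reaches the top of its assumed range. The intended message that CEUS could replace CECT would then rest on a few dozen metastatic patients at most.

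**Working it through.** **Inputs from the Sample size section.** 65 CECT patients; 10% dropout; prevalence 25–50%, read as the share of patients with metastases; sensitivity 90% for CECT and at most 95% for CEUS. Two-sided 0.05 is from Data analysis.

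**Inputs assumed because the article does not give them.** The overlap between the two reads, taken from independent to fully nested (CEUS finds everything CECT finds). Lesions per metastatic patient, taken as 3 to 3.7; the upper value is 99/27 from a small study cited in the Discussion.

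**1. Can 65 be reproduced?** No sensitivity calculation in the superiority direction gives 65. An AUC calculation can. With a binormal paired comparison of 0.75 against 0.95, 25% prevalence, an assumed between-modality correlation of 0.5, two-sided 0.05 and 80% power, 58 patients are needed, and 58/0.9 = 64.4, rounded up to 65. Neither the pairing of AUCs nor the correlation is stated, so this is a back-fit and not a reproduction. AUC gaps of 0.10 (0.75 vs 0.85, or 0.85 vs 0.95) need 123 to 263 patients at correlation 0.5, dropout included.

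**2. Metastatic patients available.** 65 × 0.9 = 58.5. Times 0.25 gives 14.6; times 0.50 gives 29.3. That is about 14–29. CECT at 90% sensitivity is expected to miss only about 1.5 to 2.9 of them.

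**3. Patient-level McNemar power, 95% vs 90%.** With d = 0.05 and discordant proportion ψ:
- independent reads: ψ = 0.95 × 0.10 + 0.90 × 0.05 = 0.095 + 0.045 = 0.14
- nested reads: ψ = 0.05

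Power = Φ[(d√n − 1.96√ψ)/√(ψ − d²)].
- n = 14, ψ = 0.14: Φ[(0.187 − 0.733)/0.371] = Φ(−1.47) = 7%
- n = 14, ψ = 0.05: 12.5%
- n = 29, ψ = 0.14: 10.5%
- n = 29, ψ = 0.05: Φ[(0.269 − 0.438)/0.218] = Φ(−0.78) = 22%

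**4. Patients needed for 80% at patient level.** n = (1.96√ψ + 0.842√(ψ − d²))²/d².
- nested: 154.6, about 155 metastatic patients; 154.6/(0.50 × 0.9) = 344 CECT patients at 50% prevalence
- independent: 437.2 metastatic patients; 437.2/(0.25 × 0.9) = 1,943 CECT patients at 25% prevalence

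All 330 patients would supply 330 × 0.9 × 0.50 = 148.5 metastatic patients at most, just short of the smallest requirement.

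**5. The planned paired t-test on lesion counts.** Simulated with 58 patients, each lesion detected with probability 0.95 or 0.90, no within-patient clustering. Ranges run from independent to nested reads.

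| Lesions per metastatic patient | 25% prevalence | 50% prevalence |
|---|---|---|
| 3 | about 10–12% | about 21–54% |
| 3.7 | about 12–19% | about 25–68% |
| 5 | about 15–33% | about 34–85% |

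Allowing for simulation error and the choice of count distribution, power at 3–3.7 lesions is about 9–20% at 25% prevalence and 21–68% at 50%. It passes 80% only at 50% prevalence, about 5 or more lesions and fully nested reads. If all 65 were evaluable, 3.7 lesions would give about 13–25% and 29–76%.

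**6. Precision.** The 95% half-width of the patient-level sensitivity difference is 1.96√((ψ − d²)/n). With independent reads it is 0.194 at n = 14 and 0.135 at n = 29, so about 13–19 points. Nested reads would narrow this to about 8–11 points, still wider than the 5-point best case.

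**The case against.** Four points can be made for the plan.

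First, the planned test counts lesions, and several lesions per patient carry more information than one result per patient. This stands. A reader might infer from the patient-level figures that power is below about 25% throughout, or that a non-significant result is close to certain. The documents do not support either: the count test reaches about 68% in a favourable case and passes 80% in an extreme one. Clustering of lesions within patients could lower these figures, but its size is not given either.

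Second, a reader might call 65 an arithmetic error. That is not shown, because an AUC contrast of 0.75 against 0.95 can yield it. What stands is that the contrast is of a different quantity, and a gap of 0.20 sits poorly beside assumed sensitivities of 90% and at most 95%.

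Third, Data analysis names no AUC comparison, which invites the inference that none will be done. The article is condensed and accuracy against CECT is a secondary endpoint, so an AUC analysis may be specified elsewhere. Its absence here is not the point.

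Fourth, 65 is a minimum. More CECT scans would help, but the power claim is attached to 65, and at patient level even all 330 patients fall slightly short of the most favourable requirement.

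**Conclusion.** The concern holds as a mismatch between the basis for 65 and the endpoint that decides success. For lesion detection, the stated inputs do not give 80% or 90% power against CECT with 65 patients. At the best assumed sensitivities, power is about 7–22% at patient level. For the planned count test it is about 9–20% at 25% prevalence and 21–68% at 50%.

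The count-test ranges depend on 3–3.7 lesions per metastatic patient, independent to nested reads and no clustering, none of which the article fixes. The direction of the conclusion depends on none of them short of the extreme combination of 50% prevalence, about 5 or more lesions and fully nested reads. For any CEUS sensitivity below 95% the advantage is smaller still, and at or below 90% there is none to detect.

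**What to change.** In Sample size, withdraw the 80% or 90% power claim for the CECT comparison on lesion detection. State instead the achieved power as a range with its assumptions (prevalence, lesions per patient, read overlap), and the expected 95% half-width of about 13–19 points for the patient-level sensitivity difference under independent reads. Say that the AUC basis applies, if at all, only to the diagnostic-accuracy comparison, and give the AUC pair and correlation used.

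In Primary endpoint and Secondary endpoint, base the confirmatory success claim on CEUS versus conventional ultrasound. Report CEUS minus CECT as a paired estimate with a 95% confidence interval, and make no superiority or replacement claim from the CECT subset.

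The cost is wording in three sections and a less favourable CECT claim. No extra patients are needed. Enlarging the CECT subset is an alternative if the sponsor wants to keep a confirmatory CECT claim, but it would need a new calculation on the lesion-detection endpoint.
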